### Statistical analysis

Statistical analyses will be performed using SPSS statistics. All data will be checked for normal distribution using the Kolmogorov test. For normally distributed data, continuous variables will be analyzed using the independent Student’s *t* test and the variables will be presented as mean ± standard deviation (SD). Non-normally distributed data will be compared using the Mann-Whitney *U* test where appropriate, and data will be presented as the median and interquartile range (IQR). For categorical variables, cross-tabulation and the Pearson chi-squared test will be applied and variables will be allegorized as number and/or percentage of the total. To compare the continuous measurements of HR, NIPD, and SpO_2_ between the groups, the area under the curve (AUC) for each value will be calculated over the different measurement time points during the procedure. A *p* value <0.05 will be considered statistically significant. Confidence intervals will be reported where appropriate.

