### Participants

#### Number of patients needed

Alfentanil reduces the required hypnotic dose of propofol by 20–50% at fairly low doses according to the literature [5]. A 15% reduction in propofol requirement when using esketamine instead of alfentanil would reflect a total dose reduction of propofol by up to 65%, which is not only a statistically significant but also a clinically relevant difference.

The sample size calculation is based on retrospectively obtained observational data from previous ERCPs, collected in our hospital sedation database. The primary endpoint is the difference in the dose of propofol used. The mean dosage of propofol during ERCP was 580 mg, with a standard deviation of 190 mg. We will need to study 76 subjects in each group, given power of 0.80 and type I error of 0.05, to reduce propofol requirement by about 15%. Considering a dropout rate of 10%, the estimated sample size will be 83 patients per group, thus a total of 166 patients will be randomized.

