### Intervention

All patients are fasted at least 6 hours before ERCP. Antibiotic prophylaxis is given according to hospital standards. As a standard procedure, diclofenac 100 mg is administered rectally immediately before the procedure to reduce post ERCP pancreatitis [6]. Procedural sedation is performed by anesthesia nurses trained in the standards of care for procedural sedation and analgesia (PSA) according to the Dutch national guidelines. An anesthesiologist is available for liaison, supervision and emergency help. Insufflation of the duodenum during ERCP is with CO_2_ instead of air, to reduce peri-procedural pain and abdominal distension.

Patients are asked to complete a questionnaire before the procedure to assess baseline pain, drowsiness, nausea, perception, and mood using a visual analog scale (VAS) (0 = 100). Baseline assessments of the Modified Observer’s Assessment of Alertness/Sedation Scale (MOAA/S), the Aldrete recovery score and measurements of heart rate (HR), non-invasive blood pressure (NIBP), respiratory rate (RR), and oxygen saturation (SpO_2_) are recorded.

After placement of an intravenous line, an infusion of 500 ml NaCl 0.9% is started at the rate of 250 ml/h. Five minutes before insertion of the endoscope, glycopyrrolate 0.2 mg, and lidocaine 50 mg are administered intravenously. Then patients are asked to place themselves into the prone or semi-prone position. From the start of sedation till the end of the endoscopic procedure, 2 L/min of oxygen are administered by nasal cannula, and HR, SpO_2_, RR, electrocardiogram (ECG), NIBP, end-tidal carbon dioxide (etCO_2_) and sedation level measured by the MOAAS/S are collected at 5-minute intervals. An independent, blinded observer collects research data.

Both groups are sedated by a propofol TCI system (Propofol 1% MCT Fresenius). TCI means a weight pre-programmed system using the Marsh pharmacokinetic model to attain a specific estimated propofol plasma target level [7]. We start propofol TCI in both groups with a targeted plasma level of 1.5 μg/ml. Reaching this plasma level, group K is treated with esketamine (Ketanest S, Pfizer) 150 μg/kg and group A is treated with alfentanil (Rapifen, Janssen-Cilag) 2.0 μg/kg. After 2 min propofol TCI is stepped up - if needed - to a maximum targeted plasma level of 2.5 μg/ml.

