Before starting the endoscopic procedure, patients are assessed for their level of sedation using the MOAA/S scale yielding at a score <2. The modified form of the MOAA/S scale uses not only the responsiveness component of the original scale (awake (5) - unresponsive (1)) but is extended with assessment of painful stimuli. As reaction to painful stimuli are still possible at anesthetic levels that block reactions to verbal commands, prodding, or shaking they can be used to assess deeper sedation levels.

If MOAA/S is > 2, e.g. the patient is too responsive to tolerate the procedure; additional sedation is provided with TCI increments of 0.5 μg/ml plasma target level. These very small steps are performed in order to avoid deep sedation. For every step up of propofol TCI, additional esketamine 50 μg/kg or alfentanil 1 μg/kg is added. Maximum dosage is 500 μg/kg ketamine or 7.5 μg/kg alfentanil.

Total dosage of propofol, alfentanil, and esketamine and the time of the total procedure and length of time between the end of the procedure (removing the scope) till reaching an MOAAS score > 4 and the declaration that the patient is ready for transport to the recovery unit, is noted.

At arrival in the recovery room, monitoring is limited to SpO_2_, RR, ECG, and NIBP only. Recovery from anesthesia and the return of psychotomotoric fitness is assessed using the modified Aldrete score at arrival and 15, 30, 45, and 60 min later. This score describes the patient’s motoric activity, mechanical respiratory function, oxygen saturation, blood pressure, and consciousness and is designed to assess patient recovery after sedation. The total score is 10 [8]. During the time in the recovery room patients have to complete the identical questionnaire they completed at baseline, on pain, drowsiness, nausea, perception, and mood, using a VAS (0 = 100). Following daily standards, post-procedural pain is indicated as VAS > 40 and is treated with 2 mg morphine intravenously; nausea indicated by a VAS > 40 will be treated with 4 mg ondansetron intravenously.

Patients have to stay for at least 1 h in the recovery room. “Ready for discharge” is declared when an Aldrete score ≥ 9 or similar to the pre-procedural score is reached. The patient must be wide awake without suffering from side effects (e.g. nausea, dizziness), with stable hemodynamic signs, and able to ambulate without assistance. A follow-up telephone call will take place on the next day after the procedure.

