### Secondary objectives

#### Definition of secondary endpoints

Secondary endpoints focus on the satisfaction of patients and endoscopists with sedation and side effects, and on hemodynamic stability and safety, which is reflected in the number of respiratory and cardiovascular events.

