#### Questionnaires

Before ERCP, after the procedure and arrival on the recovery unit, and on the following day patients are asked to complete questions on pain levels, drowsiness, nausea, perception, and mood using VAS scales (0 = 100). Pain intensity will be assessed by using a 100-mm VAS scale, with 0 = no pain and 100 = worst possible pain. Nausea will be measured by a VAS scale, with 0 = none and 100 = vomiting. Perceptual change will be assessed in five categories (i.e., body, surroundings, time, reality, colors, and sounds) by using a VAS scale anchored by “normal” at one end and “extremely” at the other end. Mood states are ranked between 0 and 100 in five categories: anxious/composed, hostile/agreeable, depressed/elated, tired/energetic, and confused/clearheaded) (modified from Mortero et al. [9]).

The day after the procedure patients are contacted by telephone to assess post-procedural satisfaction. The patient is asked the same questions from part one and two of the patient questionnaire. Patients are also be interviewed about their total satisfaction with the procedure, about their physical activity level using a 5-point rating scale: 1 = chair bound; 2 = minimal (i.e. can go to the bathroom); 3 = moderate (i.e. can go around the house and garden); 4 = almost normal; and 5 = normal, and they are asked if they would recommend this sedation regime to one of their friends. Endoscopists have to fill in questionnaires on their estimation of pain, sedation, ease of performance, and satisfaction with the procedure.

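### Pain, drowsiness, nausea, perception and mood are scored at baseline, but the stated tests give that baseline no role, which costs precision on secondary endpoints

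*Protocol article*

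**What the plan says.** The Intervention section sets the baseline measurement: "Patients are asked to complete a questionnaire before the procedure to assess baseline pain, drowsiness, nausea, perception, and mood". In the recovery room, "patients have to complete the identical questionnaire they completed at baseline, on pain, drowsiness, nausea, perception, and mood". The Questionnaires section adds a telephone contact the next day: "The patient is asked the same questions from part one and two of the patient questionnaire". The same items are therefore scored at three times, the first before any sedation.

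The scores serve the secondary objectives: "Secondary endpoints focus on the satisfaction of patients and endoscopists with sedation and side effects".

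The Statistical analysis section gives a single rule for continuous variables. "For normally distributed data, continuous variables will be analyzed using the independent" Student's t test; otherwise, "Non-normally distributed data will be compared using the Mann-Whitney" U test. It names no covariate, change score or repeated-measures model for the questionnaire scores. The only special treatment of repeated data is an area under the curve for heart rate, blood pressure and oxygen saturation during the procedure.

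**The concern.** A two-sample t or Mann-Whitney test on a recovery score uses only that score. If patients who start with more pain or lower mood also tend to end with more pain or lower mood, that predictable part of the spread stays in the error term. Adjusting for the baseline score removes it. Adjustment also corrects the estimate for whatever baseline difference chance leaves between the groups.

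This matters because these scales are the patient-reported measure of psychotomimetic and other side effects, which the Background names as the potential problem with esketamine. The stated aim is to keep satisfaction at the same level, so a null result on these scales is likely to be read as reassurance, and a less sensitive test makes a null result easier to obtain. The trial was sized on propofol dose alone, so the VAS comparisons have no power calculation of their own.

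**Working it through.** **Inputs from the protocol article (Number of patients needed).** "The mean dosage of propofol during ERCP was 580 mg, with a standard deviation of 190 mg"; a reduction of about 15%; 76 per group, "given power of 0.80 and type I error of 0.05".

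**Inputs assumed.** The document gives no effect size for the VAS scores and no correlation r between baseline and later scores. I take a difference of 0.4 SD and r = 0, 0.3, 0.5 and 0.6.

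**Step 1: reproduce the plan's own figure.** The difference is 0.15 × 580 = 87 mg, or 87/190 = 0.458 SD. The two-sided normal approximation at 0.05 and 80% power gives 74.87, so 75 per group. The t-test calculation gives 75.84, so 76. The stated 76 reproduces, and I use it below.

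**Step 2: power with and without adjustment.** ANCOVA multiplies the residual variance by 1 − r², so a 0.4 SD difference behaves like 0.4/√(1 − r²) SD. Unadjusted two-sided t-test power at 76 per group is 0.688. The last column is 76/(1 − r²), the number per group that an unadjusted test would need for the same precision.

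| r | 1 − r² | Effective difference (SD) | ANCOVA power | Equivalent unadjusted n per group |
|---|---|---|---|---|
| 0 | 1.00 | 0.400 | 0.688 | 76 |
| 0.3 | 0.91 | 0.419 | 0.729 | 84 |
| 0.5 | 0.75 | 0.462 | 0.808 | 101 |
| 0.6 | 0.64 | 0.500 | 0.865 | 119 |

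**Step 3: check by simulation.** With 6,000 normal data sets at 76 per group and r = 0.3, 0.5 and 0.7, the type I error was 0.046 to 0.054 unadjusted and 0.048 to 0.051 adjusted. At r = 0.5, with a 0.4545 SD effect (one for which the unadjusted test has about 80% power), power was 79% unadjusted and 89% adjusted. Both methods hold their level; they differ in precision.

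**Step 4: chance imbalance.** The standard error of a baseline difference is √(2/76) = 0.162 SD, so an imbalance of about two standard errors is 0.32 SD. It shifts the unadjusted difference by r × 0.32: 0.10 SD at r = 0.3, 0.16 SD at r = 0.5 and 0.19 SD at r = 0.6. Given that particular imbalance, the two-sided false-positive rate of the unadjusted test is about 8%, 13% and 16%. Averaged over all randomisations it stays at 5%.

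**Step 5: would change scores do instead?** The variance factor of a change score is 2(1 − r): 1.4 at r = 0.3, 1.0 at r = 0.5 and 0.8 at r = 0.6. The ANCOVA factors are 0.91, 0.75 and 0.64. Change scores are less efficient than ANCOVA at each of these values, and worse than ignoring the baseline whenever r is below 0.5.

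**The case against.** **The article does not say that raw scores are tested.** The rule is generic and never mentions the VAS scores. A t test on change from baseline would fit its wording and would use the baseline. This stands as a limit on what can be claimed: the baseline has no stated role, which is not the same as a statement that it is discarded. It does not remove the point, because no change score is mentioned and step 5 shows that change scores are not a safe remedy.

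**Covariates are commonly left to a statistical analysis plan that is not shown.** That would answer a complaint about silence. Here the article names the test family for continuous data, and neither test takes a covariate.

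**The benefit is assumed.** This largely stands. The document gives neither r nor the effect size, nor any baseline data. Entry is limited to elective ERCP in ASA I–III patients, with chronic pain, psychiatric history and drugs acting on the central nervous system excluded, which may narrow the baseline spread. Perception and nausea are anchored at normal and at none, so they may sit at the floor before sedation, and adjustment would then gain almost nothing. These are also scales on which a psychotomimetic harm would be sought. The figures assume normal errors and say nothing about the size of the gain on skewed or zero-heavy scales.

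**A reader might infer bias, or that the trial would miss harm from esketamine.** The documents support neither. Under randomisation the unadjusted comparison is unbiased and keeps its 5% level, as step 3 shows, and its standard error already allows for chance imbalance on average. How much sensitivity to harm is lost depends on correlations that nobody has yet reported.

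**Conclusion.** The point holds as an improvement in efficiency, not as an error of validity. The three-time collection of the same items and a rule limited to two-sample tests are both stated, and nothing connects the baseline to the comparison.

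Under the assumptions above, power would rise from 0.69 by nothing at r = 0 and to 0.86 at r = 0.6. Pain and mood probably stand to gain most, perception and nausea perhaps nothing. Only secondary endpoints are affected. The primary endpoint, total propofol dose, has no baseline value, so its analysis and the planned 76 per group (83 with dropout) do not change.

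**What to change.** Add to the Statistical analysis section that each recovery and next-day VAS score will be compared between groups by ANCOVA, with treatment, centre and the patient's own baseline score on that scale as terms, and reported as an adjusted difference with a 95% confidence interval. For strongly skewed or zero-heavy scales, name a proportional-odds model with the same covariates in place of Mann-Whitney.

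The cost is analysis wording, to be settled before any unblinded analysis. The questionnaires already supply the data, and no patient, visit or change to the sample size is needed.

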## Background

Endoscopic retrograde cholangiopancreatography (ERCP) is a complicated, often painful gastrointestinal procedure. It is used for diagnostic purposes in biliary and pancreatic disease and also for therapeutic interventions such as sphincterotomy, gallstone extraction, and biliary and pancreatic duct stenting. Because any movement of the patient could importantly affect success of the ERCP, procedures are usually performed under deep sedation or even general anesthesia with the patients in the semi-prone or prone position [1–3]. Over the last decade the combination of propofol and an opioid has become the preferred sedative regime during ERCP in many countries, despite known side effects.

Esketamine, the s-enantiomer of ketamine - is not only a well-known sedative, but also has strong analgesic properties. Furthermore, its sympathomimetic qualities can counteract the hemodynamic depression of propofol and so reduce the risk of cardiovascular and respiratory depression during sedation. A potential problem of esketamine could be its psychotomimetic effects, such as visual disturbances, vertigo, or nausea that could compromise patient satisfaction. There is still little evidence of an improved safety profile of a combination of propofol/esketamine and it is still open to discussion whether esketamine psychomimetic effects play a significant role in outpatient treatment.

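### As written, the AUC used to compare heart rate, blood pressure and SpO2 is not divided by monitored time, so it mixes vital-sign level with procedure length and loses power, almost all of it for SpO2

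*Protocol article*

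**What the plan says.** The Statistical analysis section names the summary measure and its purpose. "To compare the continuous measurements of HR, NIPD, and SpO_2_ between the groups" (the second item is evidently NIBP), "the area under the curve (AUC) for each value will be calculated over the different measurement time points during the procedure". For normally distributed data, "continuous variables will be analyzed using the independent Student’s *t* test"; otherwise the Mann-Whitney U test applies. Neither test adjusts for anything.

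The Intervention section sets the window: "From the start of sedation till the end of the endoscopic procedure", vital signs "are collected at 5-minute intervals". The same section records "the time of the total procedure and length of time between the end of the procedure", so duration is available for every patient, but the analysis section does not use it. The Background describes ERCP as diagnostic and also as a route to "therapeutic interventions such as sphincterotomy, gallstone extraction, and biliary and pancreatic duct stenting", a mix in which procedures of different length are to be expected.

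The article mentions no division by monitored time, no common window, no threshold or baseline-corrected AUC and no adjustment for duration.

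**The concern.** An AUC over a window that ends when the procedure ends grows with the length of the procedure. Two patients with the same constant heart rate of 80 score 2400 after 30 minutes and 4800 after 60. For SpO2 the ordering can reverse: 90% held for 40 minutes scores 3600, and 97% held for 20 minutes scores 1940, so the less well oxygenated patient gets the higher value.

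A two-group test on such a quantity carries the spread of procedure length as noise. A real difference in heart rate, pressure or saturation may then be missed. If one sedation regimen also changes how long the ERCP takes, the difference in length would appear as a difference in vital signs. This AUC is the article's only stated comparison of the continuous vital signs over time.

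**Working it through.** **Plan figures used.** The article gives no figure for the AUC comparison. Its group size is used here and can be reproduced: 15% of 580 mg is 87 mg, and 2 × (1.960 + 0.842)² × 190² / 87² = 74.9. The t-distribution version gives 75.8, hence the stated 76 per group.

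**Assumed inputs (none is in the article).** Between-patient mean and SD of the level, and true difference: heart rate 80, SD 12, difference 8; mean arterial pressure 90, SD 13, difference 6.5; SpO2 96.5, SD 2, difference 1.5. Level and duration are independent. The CV of duration runs from 10% to 50%. The mean duration cancels out.

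The nearest documented indicator of spread is the CV of total propofol dose, 190/580 = 33%. That also contains weight and target level. Removing an assumed 20% for weight and 15% for target level leaves √(0.328² − 0.20² − 0.15²) = 21%. This is a rough guide, not an estimate of the duration CV.

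**Formulas.** Let μ and σ be the mean and SD of the level, and c the CV of duration.

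- Share of AUC variance due to duration = c² / [(1 + σ²/μ²)(1 + c²) − 1].
- In units of mean duration, the variance of the AUC in an arm is v = μ²c² + σ²(1 + c²). For a true difference δ, z = δ / √((v₁ + v₂)/76), and power = Φ(z − 1.96) + Φ(−z − 1.96).

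**Worked cases.**

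- SpO2, c = 10%: v₁ = 93.12 + 4.04 = 97.16; v₂ (mean 98) = 96.04 + 4.04 = 100.08. SE = √(197.24/76) = 1.611, z = 0.931, power 15%.
- Heart rate, c = 20%: v₁ = 256.00 + 149.76 = 405.76; v₂ (mean 88) = 309.76 + 149.76 = 459.52. SE = √(865.28/76) = 3.374, z = 2.371, power 66%.

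| Duration CV | HR: share / power | Pressure: share / power | SpO2: share / power |
|---|---|---|---|
| 10% | 31% / 92% | 32% / 70% | 96% / 15% |
| 15% | 49% / 80% | 51% / 55% | 98% / 10% |
| 20% | 63% / 66% | 65% / 42% | 98.9% / 8% |
| 33% | 81% / 37% | 82% / 22% | 99.6% / 6% |
| 50% | 90% / 20% | 91% / 13% | 99.8% / 5% |
| AUC divided by time | power 98% | power 87% | power over 99% |

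Simulated t tests agree to within about a percentage point (16% for SpO2 at a CV of 10%; 92%, 66%, 37% and 20% for heart rate at 10%, 20%, 33% and 50%).

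**Break-even.** Duration accounts for half of the variance when its CV about equals that of the level: 12/80 = 15% for heart rate, 13/90 = 14% for pressure, 2/96.5 = 2% for SpO2.

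**False-positive rate.** With equal levels and the same duration distribution in both arms, simulation of heart rate and SpO2 gave p < 0.05 in 4.8% to 5.3% of trials over CVs of 10% to 50%. With equal levels but one arm's procedures systematically 10% longer, the undivided AUC gave p < 0.05 in 64% / 36% / 20% of trials for heart rate, 65% / 35% / 20% for pressure and 82% / 43% / 22% for SpO2, at duration CVs of 20% / 33% / 50%. The time-weighted mean stayed at about 5%.

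**The case against.** The strongest reply is that the article never says the AUC is undivided. It condenses a full protocol, and a SAP that is not shown could scale the AUC or fix a window. This stands as a limit: one cannot conclude that the final analysis will use the undivided value. But the article does not defer the measure. It names one and defines its time base, and that definition followed as written gives level times duration.

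Three stronger readings are tempting and are not supported:

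- A reader might infer that a chance imbalance in procedure length produces false positives. It does not raise the error rate: under randomisation with equal duration distributions the 5% level already covers it. The raised rates above need a systematic effect of treatment on duration, and the article neither states nor predicts one.
- A reader might infer that all three signals mostly measure procedure length. For SpO2 this holds over the whole range examined. For heart rate and pressure it depends on a duration CV above about 15%; at 10%, heart rate keeps 92% power for the assumed 8-beat difference.
- A reader might infer that the trial's safety conclusions rest on this AUC. The definition of secondary endpoints ties hemodynamic stability and safety to the number of respiratory and cardiovascular events, which are counted by consensus definitions. The AUC appears in no endpoint definition.

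The sizes also depend on assumed SDs and differences. The dependence of the AUC on duration does not; it follows from the definition.

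**Conclusion.** The point holds as a should-fix on a supportive secondary comparison. The stated AUC over a patient-specific window is level times duration. For SpO2 that leaves a comparison with almost no power (about 5% to 16%, against over 99%), and this does not hinge on where in the 10% to 50% range the duration CV lies. For heart rate and blood pressure the loss runs from modest at a CV of 10% to severe at 33% or more. The harm is mainly lost power, so an absence of difference on this measure would say little about the vital signs. Spurious differences are a risk only if treatment changes procedure length. The primary endpoint, the sample size and the event counts are unaffected. The figures rest on 76 per group, independence of level and duration, and the assumed means, SDs and differences listed above.

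**What to change.** Replace the AUC sentence with wording such as: For each patient, the AUC of HR, NIBP and SpO2 from the start of sedation to the end of the endoscopic procedure is divided by the observed time between the first and last reading, and this time-weighted mean is compared between groups. A mixed model of the 5-minute readings would serve equally well. State that the undivided AUC is not tested. If the full protocol or SAP already divides by time, say so in the article's wording.

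The cost is one sentence. The readings and the procedure time are already collected, so no new data and no more patients are needed.
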